## Abstract

**Background:**

Chronic Obstructive Pulmonary Disease (COPD) is a prevalent debilitating long term condition. It is the second most common cause of emergency admission to hospital in the UK and remains one of the most costly conditions to treat through acute care.

Tele-health monitoring offers potential to reduce the rates of re-hospitalisation and emergency department visits and improve quality of life for people with COPD. However, the current evidence base to support technology adoption and implementation is limited and the resource implications for implementing tele-health in practice can be very high. This trial will employ tele-health monitoring in a preventative capacity for patients diagnosed with early stage COPD following discharge from hospital to determine whether it reduces their need for additional health service support or hospital admission and improves their quality of life.

**Methods/Design:**

We describe a pilot study for a two arm, one site randomized controlled trial (RCT) to determine the effect of tele-health monitoring on self-management, quality of life and patient satisfaction. Sixty patients who have been discharged from one acute trust with a primary diagnosis of COPD and who have agreed to receive community clinical support following discharge from acute care will be randomly assigned to one of two groups: (a) Tele-health supported Community COPD Service; or (b) Usual Care. The tele-health supported service involves the patient receiving two home visits with a specialist COPD clinician (nurse or physiotherapist) then participating in daily tele-monitoring over an eight week period. Usual care consists of six home visits to the patient by specialist COPD clinicians again over eight successive weeks. Health status and quality of life data for all participants will be measured at baseline, on discharge from the service and at six months post discharge from the service.

**Discussion:**

The tele-health service under study is a complex service delivered through a collaboration between local authority and health care partners. The implementation of this service demanded significant changes to established working patterns and has been a challenging process requiring considerable planning - a challenge that many providers are likely to face in the future.

**Trial registration:**

Current Controlled Trials ISRCTN68856013

## Background

### COPD

Chronic Obstructive Pulmonary Disease (COPD) is the fifth biggest killer disease in the UK [1]. It is also the second most common cause of emergency admission to hospital and one of the most costly in-patient conditions [2], accounting for £587 m of the £1.08bn spent on hospital admissions for lung disease by the NHS [3]. The current prevalence of COPD in the UK is around 1.5% of the population (approximately 900,000 people), with the condition now being of equivalent incidence in both men and women [4]. The National Institute for Health and Clinical Excellence (NICE) [5] estimates the direct cost of COPD at more than £982 million per year when accounting for indirect costs.

Primarily a smoking related disease, COPD is a long term condition that affects one in six smokers aged over 45 years and is characterized by a chronic, progressive decline in lung function. In the early stages of the disease patients are largely free of symptoms, but as the disease progresses patients may become house-bound, socially isolated and depressed. Patients with COPD thus experience poor quality of life with impaired emotional, social and physical functioning [6]. Exacerbations in symptoms (characterized by increased airway and systemic inflammation and significant deterioration in lung function) occur with increasing frequency and often require hospital management.

### Care delivery model

There is a clear case for the redesign of NHS services for patients with chronic diseases. In 2002, a Cochrane review [5] concluded that a 'hospital at home' approach was a safe and effective option for certain patients with COPD with this recommendation being included within subsequent NICE Guidelines. The NHS Modernisation Agency [7] also proposed that in the future, patients with chronic diseases should no longer occupy acute beds, but rather be treated in a community setting, or supported at home. A key message from the National COPD Patient survey [8] was the need to prioritise personalized COPD planning and self management. Furthermore, in their 2004 annual report [9], the Foundation for Assistive Technology UK (FAST) suggested that chronic disease services needed to be redesigned around patients with a focus on prevention, assessment and self-management.

Tele-health monitoring is defined as the remote exchange of physiological data between a patient at home and medical staff to assist in diagnosis and monitoring. It includes (amongst other things) a home unit to measure and monitor temperature, blood pressure or other vital signs for clinical review at a remote location (for example, a hospital site) using phone lines or wireless technology [10]. The use of community based medical monitoring technology offers real potential for people with long term conditions in that it removes the physical location aspect of health care. Consequently it is believed that effective use of tele-health could lead to significant cost savings [11].

Research has demonstrated that timely and effective treatment and support can shorten COPD exacerbations, leading to a reduction in the need for hospital admission and patient length of stay, resulting in improved outcomes and quality of life for patients [1]. A comprehensive systematic literature review on tele-health for COPD was undertaken by the King's Fund Whole System Demonstrator Action Network [12]. Of the nine COPD studies included in this review, one small randomized controlled trial and three observational studies compared home tele-monitoring and five trials compared telephone support with usual care. Home tele-monitoring and telephone support were found to reduce the rates of re-hospitalization and emergency department visits.

The evidence for community-based tele-health health services is more limited. We are aware of one RCT currently in progress which should be reported upon in 2011 [13]. This is investigating the clinical and cost-effectiveness of using tele-health technology for supported self-monitoring of patients with COPD. This two arm trial is comparing tele-health monitoring with standard care for patients with moderate to severe COPD, recruited from Lothian general practices (GPs) who have been admitted to hospital with an exacerbation of COPD in the previous six months.

No robust studies have been located which examine the use of tele-health monitoring of people in the earlier stages of the condition.

### Local context

The RCT will take place in a region covered by one PCT which has a high incidence of COPD which can be traced to both its coal mining history and the relatively high levels of smoking by the population [14]. It is ranked as one of the most deprived local authorities in the Index of Multiple Deprivation [15]. The high levels of deprivation are associated with poor diet and other adverse lifestyle factors, with smoking being one such factor [16]. The PCT has been recognized as one of the best in the country at detecting COPD by the Eastern Region Public Health Observatory and has been placed in the top 10 for the detection of COPD against all other Primary Care Trusts in England [17].

New service developments have been put in place in the location for this research in order to provide optimal management for people with COPD following hospital discharge. A new Community COPD Service was introduced in May 2009, to manage people with early stage COPD for up to eight weeks following hospital discharge. The remit of the new service is to encourage self-management by patients including education, medication management and lifestyle changes, with the aim of preventing further admissions and improving patient quality of life. In May 2010, the PCT introduced a tele-health supported Community COPD Service. Using the technology, which is personalized to each patient's condition, patients are enabled to monitor their own signs and symptoms, with alerts being provided to community clinicians should any recorded data fall outside expected parameters or if the patient fails to provide data. Thus, community clinicians only need to make additional patient visits to those planned on the care pathway if an alert is raised. Service commissioners and providers identified that this was an opportune time to investigate the impact of tele-health technology compared to traditional methods of delivering post discharge community clinical services. Consequently a pragmatic RCT has been planned with key staff.

## Methods/Design

Given the complexity of the care pathway, the newness of the services and the lack of population-based data on which to base the sample size calculation, in accordance with MRC Guidance, a pilot study will be undertaken. This pilot study will be conducted over a three month period and will operate as a 'mini-trial', testing all elements of the definitive trial. It will use the research methodology developed for the definitive trial in terms of inclusion/exclusion criteria, care pathways, data collection tools and randomisation procedures which are outlined below.

### Design of the Definitive Trial

The definitive study will be a twelve month, single blind, two arm, randomized trial in one Primary Care Trust (PCT) in the United Kingdom. The study population will be patients discharged from acute care diagnosed with COPD who have agreed to use the Community COPD Service as part of their post hospital discharge support.

The study will test the following specific hypotheses:

1. Tele-health monitoring will reduce the proportion of patients with early stage COPD who require further hospital re-admissions to manage their COPD for the duration of, and for six months following discharge from the Tele-health-supported Community COPD Service when compared with those who received the standard Community COPD Service; and

2. Tele-health monitoring will improve the quality of life for patients for the duration of, and for six months following discharge from the Community COPD Service when compared to the standard Community COPD Service.

There are two referral routes into the Community COPD Service:

1. The acute trust employs two COPD nurses who may refer people directly to the Community COPD Service as a supportive early discharge service. Patients not wishing to use the early discharge service will remain under the care of the inpatient COPD nurses until alternative arrangements have been made. Alternatively;

2. Any member of the acute trust nursing staff may use a new telephone referral service for patients with a diagnosis of COPD, who are being discharged from any ward in the hospital. The administration team of the Community COPD Service triage each of these patients to ensure that they are eligible to utilise the service.

### Primary and Secondary Outcome Measures for the Definitive Trial

Two primary outcomes will be measured:

1. The health service primary outcome will be the proportion of patients who are re-admitted to hospital with COPD as the primary or secondary cause of their admission, either during, or six months following their discharge from the Tele-health supported or standard Community COPD Service. This will be assessed through analysis of patient-completed self-reporting diaries, which will be completed both during and for six months following the Tele-health supported or standard Community COPD Service and analysis of hospital admission data.

2. The patient-centred primary outcome will be changes in self-reported health status and quality of life as measured by comparison of the patients' St. Georges Respiratory Questionnaire score upon admission to either the Tele-health supported or standard Community COPD Service, on discharge from the service and six months after discharge from the service.

There are four secondary outcomes:

1. Proportion of patients requiring unscheduled health care support to manage their COPD (including A&E, GP or community nurse visits) either during or six months following the standard Community COPD Service. This will be collected using a paper format self-reporting diary for the standard Community COPD Service and via the monitoring system for the Tele-health supported service; and analysis of hospital, GP and community nursing activity data.

2. Cost effectiveness of intervention. Costs and outcomes will be collected for each individual patient recruited to the pilot trial. The data to be collected for cost estimates will focus on usage of emergency and home-based care by participants. Health related quality of life will be measured using the EuroQol 5 Dimensions questionnaire (EQ-5D), which can be combined with mortality data to produce quality adjusted life years (QALYs). The EQ-5 D is a simple patient completed questionnaire (typically taking less than five minutes to complete), and has been incorporated into the COPD self-completed patient diaries. To ensure monthly data collection it has been embedded into the diaries collected during weeks 1 and 5, whilst the patient is enrolled on the Community COPD Service (both modalities) and subsequent diaries completed each month following discharge from the Community COPD Service.

Data on service usage (for cost analysis) will be accessed where possible from routine data systems of acute and primary care providers and the local authority rather than being reliant upon patient recall. The pilot trial will enable the researchers to examine how feasible it is to both access and analyse this data.

3. Improved self-management of their COPD by the individual patient. This will be assessed through analysis of the results obtained from the St. Georges Respiratory Questionnaire and those from a self-completed patient satisfaction questionnaire devised for this study as described below.

4. Satisfaction with technology as part of their Tele-health supported Community COPD Service. This will be assessed through analysis of a self-completed bespoke tele-health service questionnaire to be completed by patients on the tele-health supported Community COPD Service during their final discharge visit (week 8 after leaving hospital) by Community COPD Service clinical staff.

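### The readmission window of primary outcome 1 ends six months after service discharge, a post-randomisation date, so time at risk could differ between arms; a fixed end from randomisation removes this.

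*Protocol article*

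**What the plan says.** The section on primary and secondary outcome measures defines the first primary outcome as "the proportion of patients who are re-admitted to hospital with COPD as the primary or secondary cause of their admission", with the window "either during, or six months following their discharge from the Tele-health supported or standard Community COPD Service". Hypothesis 1, under Design of the Definitive Trial, uses the same window: "for the duration of, and for six months following discharge from the Tele-health-supported Community COPD Service". The SGRQ, which is the second primary outcome, is taken on admission to the service, on discharge from it and six months after that discharge.

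The sections on recruitment and randomisation place consent and allocation at the first home visit, the day after the patient leaves hospital. Discharge from the service therefore follows randomisation.

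The protocol describes the length of the service in two ways:

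- **As a fixed eight weeks.** The abstract has tele-health patients "participating in daily tele-monitoring over an eight week period" and usual-care patients receiving "six home visits to the patient by specialist COPD clinicians again over eight successive weeks". The fourth secondary outcome puts the tele-health discharge visit at week 8 after hospital discharge, and the Diaries section also treats the usual-care programme as eight weeks long.
- **As a maximum.** Local context says the service was set up "to manage people with early stage COPD for up to eight weeks following hospital discharge".

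**The concern.** A proportion with an event is comparable between arms only if patients in both arms are observed for the same length of time. Here the end of observation is set by an event that happens after allocation and that the allocated service may influence. One arm has two home visits and daily data entry on installed equipment; the other has six clinician visits. Patients could leave the two pathways early at different rates. If they did, the arm with the shorter stays would have less time in which a readmission could be counted, and would look better for that reason alone. The direction is not predictable, and a simple proportion, unlike a rate or a time-to-event measure, does not correct for it.

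This cannot simply be left to an analysis plan. The window is part of the stated hypothesis and primary outcome, so an analysis over fixed follow-up would be an analysis of a different endpoint.

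**Working it through.** The protocol gives no readmission rate, effect size, alpha or power for the definitive trial, so it has no figure of its own to reproduce. The readmission risks below are assumptions, shown as a range.

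**Step 1: length of the window.** Six months is taken as 26 weeks.

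- Nominal stay of 8 weeks: 8 + 26 = 34 weeks in both arms, difference 0.
- If the stay can be anything from 0 to 8 weeks, the window runs from 26 to 34 weeks, a ratio of 26/34 = 0.76.

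**Step 2: effect of a shorter window on the proportion.** Let p be the risk of COPD readmission by 34 weeks, with the same constant hazard in both arms, so that there is no true effect:

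- h = −ln(1 − p)/34 per week
- proportion observed when the window is d weeks shorter: 1 − exp(−h(34 − d))
- artefact: p minus that proportion

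For p = 0.20, h = 0.2231/34 = 0.00656. With d = 2 the observed proportion is 1 − exp(−0.00656 × 32) = 0.1894, a loss of 1.06 points. For p = 0.50, h = 0.6931/34 = 0.02039. With d = 2 the observed proportion is 1 − exp(−0.02039 × 32) = 0.4792, a loss of 2.08 points.

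| Assumed 34-week risk | 1 week shorter | 2 weeks shorter | 4 weeks shorter | 8 weeks shorter (extreme) |
|---|---|---|---|---|
| 20% | 0.53 | 1.06 | 2.13 | 4.31 |
| 30% | 0.74 | 1.48 | 3.00 | 6.13 |
| 40% | 0.91 | 1.83 | 3.72 | 7.66 |
| 50% | 1.03 | 2.08 | 4.25 | 8.86 |

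Entries are percentage points by which the arm with the shorter window is flattered. The formula shortens every patient's window by d, so d should be read, approximately, as the difference between arms in mean stay. The last column would need every patient in one arm to leave at once and every patient in the other to stay eight weeks. It is only a bound.

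**Step 3: after the fix.** With the same fixed window from randomisation for everyone, d = 0 and the artefact is zero by construction.

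**The case against.** The strongest reply is that the trial pathways are described as eight weeks in both arms, so both windows are about 34 weeks and the difference is nil. The wording that makes eight weeks a maximum is background on the remit of a service launched before the trial. The protocol sets out no early-discharge rules and reports no difference in stay. All of that stands, and it makes the bias possible rather than demonstrated. It does not remove the point, because the endpoint is tied to actual discharge from the service and not to week 8, and the protocol itself plans to measure retention and adherence in the pilot.

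The size can also be challenged. A mean difference of several weeks within an eight-week service would be large. If readmission risk is highest soon after hospital discharge, cutting the end of the window loses fewer events than a constant hazard implies. Both remarks are fair. In addition, a patient who leaves the service because of a COPD readmission already has the event, so a shortened window changes nothing for that patient. Only those who leave early without a readmission matter.

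A reader might infer two stronger claims, and the protocol supports neither:

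- **That readmissions are counted only from service discharge.** They are not. The definition includes readmissions during the service, so only the end of the window depends on discharge.
- **That a patient who dies without readmission is counted as a success.** The protocol states no such rule. It mentions mortality only in connection with QALYs and is silent on death in this outcome. An unadjusted proportion of all patients would work that way by default, but the handling of death may properly be settled in an analysis plan that is not shown here.

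**Conclusion.** The point holds in a limited form. The end of the window for primary outcome 1, and the timing of the post-baseline SGRQ assessments, depend on a post-randomisation date that the protocol's own wording allows to vary. If all patients stay eight weeks, the bias is zero. Under assumed 34-week risks of 20% to 50%, a constant hazard and no true effect, a mean stay 2 weeks shorter in one arm would flatter it by about 1 to 2 percentage points, and 4 weeks shorter by about 2 to 4 points. The documents do not show that any such difference exists. This is a free improvement to the endpoint, not a demonstrated flaw in the result.

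**What to change.** Define primary outcome 1 as COPD readmission (primary or secondary cause) within a fixed period from randomisation, for example 34 weeks (8 + 26), for every randomised patient, whatever the date of leaving the service. Date the post-baseline SGRQ assessments from randomisation too, at weeks 8 and 34, and bring hypotheses 1 and 2 and the diary period into line. The descriptions of service length as eight weeks and as up to eight weeks should be reconciled. The change concerns only when outcomes are counted, not how long the service should last.

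Make the change before the pilot data are used to plan the definitive trial, so that any readmission proportion taken from the pilot refers to the window that the definitive trial will use.

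The cost is almost entirely wording. Hospital admission data are already planned as a source and do not require the patient to be in the service. For a full stay the new dates fall within about a day of the existing ones. The one practical addition is contacting patients who left the service early for their SGRQ at the set weeks. A supplementary analysis of death or COPD readmission over the same period is optional.

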#### Tele-health Intervention

Patients recruited to the Tele-health supported Community COPD Service will be taught how to use the technology to aid monitoring of their condition. The patient will be required to enter information into the tele-health equipment on a daily basis to monitor their condition. Data provided to the system will be recorded on the web server so patient compliance with using the equipment can be assessed. If the patient fails to enter information into the equipment for three continuous days the system generates an alert on the web server which is acted upon by the COPD team.

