#### Diaries

Patients recruited to the Usual Care Group will track their use of health services to assist in the management of their COPD by means of a self-reported questionnaire whilst on the eight week programme and for the subsequent six months. Patients will record whether they have contacted a health service provider because they had concerns about their COPD, who they contacted, why they contacted them and what happened as a result (telephone consultation, visit). The diaries will also be used to capture EQ5 D information on problems with mobility, self-care, usual activities, pain/discomfort and anxiety/depression.

Patients on the Tele-health supported Community COPD Service will be asked to answer the same questions as part of their routine use of the technology.

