#### Tele-health service questionnaire

Patients on the Tele-health supported Community COPD Service will be asked to complete a questionnaire on discharge from the service. The questionnaire will ascertain their opinions about the technology, the installation process, training, use of the equipment, availability of support and removal of the equipment from their home.

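### Secondary outcome 1 is open to differential ascertainment: self-report is by paper diary in one arm and by the intervention device in the other, and visits triggered by device alerts are not excluded from the events counted

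*Protocol article*

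**What the plan says.** All references are to the protocol article.

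- **Outcome.** Secondary outcome 1, under Primary and Secondary Outcome Measures for the Definitive Trial, is the "Proportion of patients requiring unscheduled health care support to manage their COPD (including A&E, GP or community nurse visits"), during the service or in the six months after it.
- **Self-report source.** The same item says this is "collected using a paper format self-reporting diary for the standard Community COPD Service and via the monitoring system for the Tele-health supported service". The Diaries section agrees: "Patients on the Tele-health supported Community COPD Service will be asked to answer the same questions as part of their routine use of the technology".
- **Common source.** The item then adds a source for both arms: "and analysis of hospital, GP and community nursing activity data".
- **Chasing of non-response.** Under Tele-health Intervention, entry is daily and "If the patient fails to enter information into the equipment for three continuous days the system generates an alert", which the COPD team acts on.
- **Alert visits.** Under Local context, "community clinicians only need to make additional patient visits to those planned on the care pathway if an alert is raised". Alerts arise from out-of-range readings or from missing data.
- **Planned visits.** Two in the tele-health arm (Abstract) and six in usual care (Abstract; Usual Care Group), each over eight weeks.
- **After the service.** The Diaries section describes a further six months of self-report for usual care only. The discharge questionnaire in the tele-health arm asks about "availability of support and removal of the equipment from their home". The readmission outcome, however, has diaries continuing for six months after either service.

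**The concern.** Two separate mechanisms can produce a difference between arms when need for care is the same.

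The first is ascertainment. In the tele-health arm the intervention is also the measuring instrument. Patients who stop answering are noticed within days and followed up. The article describes nothing similar for the paper diary, so completeness and recall may differ by arm.

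The second is the definition of an event. A clinician contact may be one of six planned visits in usual care and an extra, alert-prompted visit in the tele-health arm, where only two are planned. Nothing says whether the second kind counts as unscheduled care. If it does, part of the intervention is scored as a bad outcome in the arm that receives it.

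At stake is the between-arm comparison on secondary outcome 1: an artefact could look like harm, or could conceal a benefit. The pilot uses the data collection tools of the definitive trial, which is to follow immediately, so an artefact built in now would carry forward.

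**Working it through.** The plan gives no event rate, effect size or power for this outcome, so there is no figure to reproduce. The two mechanisms are sized on assumed rates, with no true difference between arms unless stated.

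**Inputs (all assumed)**
- p: true proportion with an event, 30% or 50%
- s: sensitivity of self-report, 0.7 or 0.9
- r: sensitivity of routine data, the same in both arms, 0 to 1
- a: share of otherwise event-free tele-health patients who have a counted alert visit, 10% to 30%

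**Formulas**
- Detected proportion: d = p × [1 − (1 − s)(1 − r)]
- Observed proportion in the tele-health arm: d + (1 − d) × a; in usual care, d

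**1. Different self-report source, alert visits not counted (a = 0).** The difference reduces to p × (s device − s paper) × (1 − r). With p = 0.5, s paper = 0.7 and s device = 0.9:

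| r | Usual care | Tele-health | Difference |
|---|---|---|---|
| 0 | 35.0% | 45.0% | +10 points |
| 0.5 | 42.5% | 47.5% | +5 points |
| 0.9 | 48.5% | 49.5% | +1 point |
| 1.0 | 50.0% | 50.0% | 0 |

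Exchanging the two sensitivities reverses every sign (−10 points at r = 0). Good routine data therefore shrink this mechanism and complete data abolish it.

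**2. Alert visits counted, routine data complete (r = 1).** Then d = p and the spurious difference is (1 − p) × a.
- p = 0.5: a = 0.10 gives 0.5 × 0.10 = 5 points; a = 0.30 gives 15 points (65% against 50%).
- p = 0.3: a = 0.10 gives 0.7 × 0.10 = 7 points; a = 0.30 gives 21 points.

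At p = 0.5 and a = 0.30, the chance of a two-sided p < 0.05 is about 21% with 30 per arm (the pilot's 60 split evenly) and about 86% with an assumed 200 per arm. The pilot would probably not reveal the artefact, whereas a larger trial could report it as a finding.

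**3. Masking of benefit (r = 1).** Suppose the true rate falls from 50% to 35%. The observed tele-health rate is 0.35 + 0.65 × a. At a = 0.20 it is 0.48. It reaches 0.50 at a = 0.15 / 0.65 = 0.23, where the benefit has disappeared.

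**4. After the fix.** With equal s in both arms and a = 0, the difference is p × 0 × (1 − r) = 0 for any p and r.

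**The case against.** The strongest reply is that secondary outcome 1 does not rest on self-report alone. Routine hospital, GP and community nursing records are used in both arms, and the questions put to patients are the same. This stands, and it limits the first mechanism: the 10-point gap above is a worst case with no routine capture. It does not close the point, because the article does not say which source decides when they disagree. In addition, its text on service-use data for the cost analysis promises routine access only where possible and leaves feasibility to the pilot.

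On alert visits, it can be said that the diary asks about contacts the patient made because of concerns, which hardly describes a visit started by the team. It is also unstated whether Community COPD Service clinicians count as community nurses, or how often an alert leads to a visit. All fair. But community nursing records are a named source and could contain those visits, so complete routine data would not help. Alert visits may also cluster in patients who have other unscheduled care; that would make a smaller than the overall alert-visit rate, which is why a is defined among otherwise event-free patients.

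Definitions are often left to the full protocol or SAP. The split of instruments by arm, however, is a stated design choice and not an omitted detail.

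Several stronger readings are tempting and not supported:
- **That tele-health patients have no diary after week 8, so the bias reverses there.** The readmission outcome has diaries for six months after either service. What remains is a conflict of wording with the Diaries section.
- **That readmission and EQ-5D are equally compromised.** Readmission also uses hospital admission data in both arms. EQ-5D has a common schedule: weeks 1 and 5 in both modalities, then monthly.
- **That the paper diary is unprompted.** The article is silent on this, and usual-care patients see a clinician six times.
- **That alert visits replace planned ones.** The article describes them as additional to the pathway.

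**Conclusion.** The concern holds for secondary outcome 1, as exposure to bias of unknown net direction and not as a demonstrated bias. Better capture by the device and counted alert visits would both count against tele-health; poorer capture by the device would favour it.

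The source difference could be worth up to 10 points on the assumed sensitivities without routine data, and 5, 1 or 0 points at routine sensitivity of 0.5, 0.9 or 1.0. The alert-visit mechanism is the more durable of the two: 5 to 15 points at a true rate of 50% if 10% to 30% of otherwise event-free tele-health patients have a counted alert visit, whatever the quality of the routine data. None of these rates comes from the article, and the second range applies only if such visits are counted, which the text neither states nor rules out.

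**What to change.** 1. Use the same diary, including EQ-5D, on the same schedule in both arms during the service and for the six months after it. Reconcile the Diaries section with the outcome section on this. Keep the device questions for care only.
2. Name routine hospital, GP and community records as the deciding source for secondary outcome 1, and hospital admission data as the deciding source for readmission, with diaries supportive in each case.
3. Define secondary outcome 1 as unscheduled care outside the Community COPD Service. Count every contact with that service, planned or alert-triggered, as resource use, so that no care is lost from the economic comparison.

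The cost is some protocol wording and, in the pilot, the existing diary for about 30 more patients (60 / 2). The downside is that tele-health patients complete a short paper form as well as using the device. The change should be made before the pilot starts.
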